## Stepwise Procedures

### Intervention

#### EMDR

Patients in the EMDR condition will receive 20 individual sessions of 60 min each, using the standard EMDR therapy protocol developed by Shapiro (47) and a further specific protocol for SUD, the CRAVEX protocol, developed by Hase (48) to treat both trauma-related symptoms and SUD symptoms, respectively.

The current standard protocol includes eight phases, briefly described below:

Patient history: The therapist assesses the patient's attachment history, medical history, physical problems and identifies traumatic events and their relationship to current symptoms. A treatment plan is developed.Patient preparation: A safe therapeutic environment is established, the theory and processes of EMDR are explained, and the therapist may try out different modalities of bilateral stimulation, including eye movements, where the patient's eyes follow the therapist's fingers moving in horizontally or diagonally across their field of vision. While eye movements are generally recommended, if they are not well-tolerated, another modality, such as tapping the back of the patient's hands or auditory tones, may be used.Patient assessment: The therapist helps the patient to bring the traumatic memory to mind and identify associated cognitions, emotions and physical sensations. The patient identifies the image which represents the worst part of the traumatic memory and an associated negative cognition, and is helped to identify a positive cognition to replace this. Finally, the patient identifies the distress level they experience upon bringing the traumatic experience and negative cognition to mind. Distress is measured using the Subjective Units of Disturbance Scale (SUD), scored from 0 (minimum disturbance) to 10 (maximum disturbance).Memory desensitization: The patient brings to mind the traumatic image, negative cognition and associated emotion and notices any physical discomfort generated in the present moment. The patient focuses on this material and a 30–40 s set of bilateral stimulation is applied, during which the patient is instructed to observe what is happening without judgment, and afterwards express what occurred. The therapist asks the patient to focus on new material without comment, assessment, or interpretation. This is repeated until no new material arises and the traumatic memory generates no distress (SUD = 0 or 1).Installing the positive cognition: The patient brings the positive cognition and original experience to mind. Further sets of bilateral stimulation are applied, causing the patient to link the positive cognition with the original memory, until the positive belief is fully installed.Body scan: The therapist asks the patient to close their eyes and focus on the original experience and positive cognition, and to notice if any sensation arises. If a negative or uncomfortable sensation is reported, the therapist will resume bilateral stimulation until it disappears. If the sensation is positive, it will be reinforced with short sets (10–12 s) of bilateral stimulation.Closure: The therapist explains possible effects following the session, such as new insights, thoughts, memories, and even dreams or nightmares, and offers recommendations about what to do in each case.Reevaluation: The therapist assesses the patient's experiences since the previous session and reevaluates the traumatic memory to confirm functional processing. If the memory has been desensitized, the therapist selects a new target of either another traumatic memory, a current trigger of distress, or a potentially threatening future event.

The CRAVEX protocol (48) will also be applied to process craving. This protocol focuses on the concept of addiction memory (AM), in which the biological effect of the drugs has a serious impact on the brain comparable to trauma, which leads to the formation of a maladaptive implicit memory which if reprocessed can decrease cravings or urges, and potentially promote access to the brain channels connected to the initial reasons the individual became addicted (49). Instead of SUD, the CRAVEX protocol uses Level of Urge (LOU), with a scale of 0 (no urge) to 10 (worst urge imaginable), referring to the urge to consume the substance. As in the standard protocol, positive and negative cognitions, emotions and physical sensations are identified but, in this case, they are associated with the last time that the subject consumed the drug. Bilateral stimulation is used until the AM is desensitized, and finally the positive cognition is installed.

#### TAU

All patients included in this study will participate in the TAU condition, comprising the standard care package offered by the Drug and Alcohol Outpatient Unit. This is a multidisciplinary unit with doctors, psychiatrists, clinical psychologists, nurses, and social workers on the staff. An individual care plan is drawn up depending on individual needs and may include follow-up psychiatric visits to evaluate clinical status and, if necessary, readjust pharmacological treatment, and psychological visits to assess and detect risk situations and prevent relapses using a non-trauma focused CBT. In no case will psychological treatment focus on PTSD. TAU also includes nurse visits for health and self-care habits and nurses may also carry out abstinence controls.

### Dropouts and Follow-Up

If a participant requires an inpatient stay due to substance misuse or an acute episode of a comorbid disorder during the 6-month intervention period, the patient will be excluded from the trial and considered as dropout because the hospital admission will mean the patient cannot continue with the EMDR psychotherapy during the acute phase. In the case of relapse during follow-up, patients will be maintained in the trial to obtain maximum information on the course of the illness.

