### Study Outcomes

The primary outcome is to test the efficacy of EMDR therapy in reducing the severity of substance use in patients with comorbid SUD and a history of psychological trauma, irrespective of whether the patient meets DSM-V PTSD criteria. Changes from baseline in the severity of substance use are measured by the Timeline Follow Back (TLFB) (31), the Severity of Dependence Scale (SDS) (32), and the Visual Analog Scale (VAS).

The secondary outcome is to test the efficacy of EMDR in improving trauma-related psychological symptoms, psychopathological symptoms, and the overall functionality in SUD patients with a history of psychological trauma. Changes in psychological trauma and dissociative symptoms are measured using the Global Assessment of Posttraumatic Stress Questionnaire (EGEP-5) (33), the Impact of Event Scale-Revised (IES-R) (34), and the Dissociative Experiences Scale (DES) (35), respectively. The type and severity of traumatic experiences are measured using the Childhood Trauma Questionnaire (CTQ) (36) and The Holmes-Rahe Life Stress Inventory (37). Changes in psychopathological symptoms are measured by the Hamilton Depression Rating Scale (HDRS) (38), Young Mania Rating Scale (YMRS) (39), and the Brief Psychiatric Rating Scale (BPRS) (40). Changes in overall functioning will be measured using the Functioning Assessment Short Test (FAST) (41).

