### Hypotheses

Patients in the EMDR group will show a reduction in the level and severity of substance use-related symptoms as compared to the TAU group.Patients in the EMDR group will show a reduction in the number of relapses as compared to the TAU group.Patients in the EMDR group will show a reduction in the severity of trauma-related symptoms as compared to the TAU group.There will be a reduction in depressive symptoms associated with a comorbid psychiatric disorder in the EMDR group as compared to the TAU group.There will be a reduction in (hypo) manic symptoms associated with a comorbid psychiatric disorder in the EMDR group as compared to the TAU group.There will be a reduction in general psychopathology symptoms associated with psychiatric comorbidity in the EMDR group as compared to the TAU group.Patients in the EMDR group will show an improvement in functioning as compared to the TAU group.

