### Statistical Analysis

The distribution of socio-demographic and clinical characteristics between groups in the baseline state will be summarized using descriptive statistics. The change in clinical and functional variables with regard to baseline evaluation at strategic points of the intervention will be analyzed using mixed-effects repeated-measures linear models, including as fixed factors time, treatment conditions and their interactions, and as a random factor the site. The differences between groups, for the categorical variables and main clinics, will be analyzed by adding covariates to the models. Those covariates that are statistically significant may be added in the same model to determine which covariates are best predictors of the response. The size of the effects will be estimated using the g of Hedges or the r of Pearson. It will be corrected for multiple comparisons. The statistical software used for the analysis will be the latest available version of R. We will conduct an intention to treat (ITT) analysis. The “Last Observation Carried Forward” (LOCF) method will be used for losses of follow-up.

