## Discussion

In recent years, the third-generation psychotherapies such as EMDR, which emerged in the 90s within the tradition of behavioral therapy (62), have gained considerable interest in both social and scientific fields due to their ability to integrate cognitive, emotional and behavioral components within the same psychotherapeutic approach, processing adverse life events and therefore ameliorating associated psychiatric symptoms. To date, preliminary evidence exists suggesting EMDR therapy is efficacious in SUD patients, thanks to previous studies done in that population (20, 63). In a more recent publication (21), a quasi-experimental study of 40 SUD outpatients found that EMDR as an add-on treatment had a pronounced effect in reducing post-traumatic and dissociative symptoms and also caused a significant improvement in the global severity of psychiatric symptoms. The aim of our trial is to provide further evidence of a positive effect of EMDR in this difficult-to-treat population in a larger RCT. In our study, we aim to treat real-world dual patients, with a wide range of substances used and varied comorbid psychiatric and somatic illnesses (except neurological disorders). In contrast to prior studies, we also include a year follow-up to test whether possible improvements are maintained. With results from a large RCT, we aim to promote trauma-oriented therapies in patients with dual disorders. Although it has been shown that there is a clear association between PTSD and addiction (64), most mental health care programs do not offer trauma-oriented therapies for patients with SUD. To understand better the relationship between the presence of traumatic events and the diagnosis of SUD, we will study several variables before, during and after treatment. We will assess variables of clinical severity, consumption and overall functioning with specific and validated instruments. In short, the potential of this study is to demonstrate the effectiveness and safety of EMDR in dual disorders. Along these lines, we could be closer to establishing an effective new psychological treatment for these patients in addition to the standard treatment. In this way, the impact of this trial is to improve the clinical evolution and prognosis and to reduce hospital admissions in SUD patients.

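### Patients admitted to hospital in the first 6 months leave the trial in both arms, so their 6- and 12-month outcomes are missing for a reason close to the primary outcome

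*Protocol article*

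**What the plan says.** The rule is in the protocol article, Dropouts and Follow-Up. It is triggered as follows: "If a participant requires an inpatient stay due to substance misuse or an acute episode of a comorbid disorder during the 6-month intervention period". The consequence is that "the patient will be excluded from the trial and considered as dropout because the hospital admission will mean the patient cannot continue" with EMDR during the acute phase. The wording refers to any participant, so it applies to the EMDR and the TAU arm alike.

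The next sentence of the same section goes the other way for later events: "In the case of relapse during follow-up, patients will be maintained in the trial to obtain maximum information on the course of the illness".

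Statistical Analysis states: "We will conduct an intention to treat (ITT) analysis". It adds that the LOCF "method will be used for losses of follow-up".

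Study Outcomes makes severity of substance use the primary outcome, measured as change on TLFB, SDS and VAS. Hypotheses adds: "Patients in the EMDR group will show a reduction in the number of relapses as compared to the TAU group". The Discussion says that "the potential of this study is to demonstrate the effectiveness and safety of EMDR in dual disorders" and names fewer hospital admissions as an intended impact.

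No section says that admitted patients are still assessed at 6 months (T2) or 12 months (T3).

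**The concern.** An admission for substance misuse is itself a poor result on what the trial sets out to measure, and it happens after randomisation. Ending participation at that point makes the outcome one of the causes of the missing data. Admission could also plausibly be affected by treatment in either direction.

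The stated reason explains why sessions are interrupted. It does not explain why outcome assessment ends, and it has no bearing on a TAU patient, who has no EMDR sessions to interrupt. The case made for keeping patients who relapse during follow-up, that their course is informative, applies equally to the first 6 months.

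If TAU has more admissions, the plan tends to understate a benefit of EMDR. If EMDR has more, it tends to overstate the benefit or mask harm on the efficacy scales. Outcomes that were never collected cannot be recovered by a later analysis.

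**Working it through.** **1. What happens to an admitted patient's data.** Two readings are open.

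- *Deletion.* Exclusion from the trial means that the patient leaves the analysis. This conflicts with the intention-to-treat statement.
- *Dropout with LOCF.* The patient stays in the analysis set with a carried value. By Tables 1 to 4, TLFB, SDS and VAS are taken at T0, T1 (3 months), T2 and T3. The repeated trauma, psychopathology and functioning scales are taken at T0, T2 and T3 only. The carried value is therefore T0 for an admission before T1. For an admission after T1 it is T1 for the three substance-use measures and still T0 for all other scales. In each case it predates the admission.

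**2. The plan's own figure.** Computation of Sample Size uses d = 0.5 and 80% power. Alpha is not stated; two-sided 0.05 is assumed, the default of the R function cited. A two-sample t-test then needs n = 63.77, so 64 per arm (power 0.801), and 128 / 0.90 = 142.2. The stated 64 per arm and approximately 142 are reproduced.

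**3. Bias under LOCF.** Let p_E and p_T be the admission proportions. Let g be the amount, in SD of change, by which admitted patients' true outcome is worse than the carried value, taken as equal in both arms. Then

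estimated minus true difference = (p_E − p_T) × g.

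With a 10-point gap, g = 0.5 gives 0.10 × 0.5 = 0.05 SD and g = 1 gives 0.10 × 1 = 0.10 SD. With p_E = p_T the bias is zero.

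**4. Worked scenarios.** The inputs are assumptions; the article gives none of them. Non-admitted TAU patients improve by 0.5 SD and non-admitted EMDR patients by 1.0 SD. Admitted patients in both arms end 1.0 to 1.5 SD worse than non-admitted TAU patients, a change of −0.5 to −1.0 SD. LOCF carries baseline (change 0), so g = 0.5 to 1.

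For admissions of 5% (EMDR) and 15% (TAU) with change −0.5:
- All followed: EMDR 0.95 × 1.0 + 0.05 × (−0.5) = 0.925; TAU 0.85 × 0.5 + 0.15 × (−0.5) = 0.35; difference 0.575.
- LOCF: 0.95 × 1.0 − 0.85 × 0.5 = 0.525.
- Deletion: 1.0 − 0.5 = 0.50.

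| Admissions EMDR / TAU | All randomised followed (SD) | Admitted deleted (SD) | Baseline carried (SD) |
|---|---|---|---|
| 5% / 15% | 0.575 to 0.625 | 0.50 | 0.525 |
| 15% / 5% | 0.275 to 0.325 | 0.50 | 0.375 |
| 10% / 10% | 0.45 | 0.50 | 0.45 |

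Under LOCF the first row understates the benefit by 0.05 to 0.10 SD and the second overstates it by the same amount. Deletion reports 0.50 in every row. In the third row it is 0.05 too high, because admitted EMDR patients are assumed not to share the benefit.

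**5. Power, deletion reading only.** If total loss from all causes were 20%, 71 × 0.80 = 56.8, so 56 complete patients per arm and power 0.746 at d = 0.5. At 30%, 71 × 0.70 = 49.7, so 49 per arm and power 0.688. Under LOCF all 142 patients are analysed and this loss does not arise.

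**The case against.** The strongest reply is that the article counts these patients as dropouts and elsewhere provides LOCF within an intention-to-treat analysis. Read together, the two sections may well keep admitted patients in the analysis set. That stands: a reader might infer that the plan flatly contradicts intention to treat, but the text does not say that admitted patients are deleted. It does not cure the problem, because the later outcome is still replaced by a value from before the admission.

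Several further points also stand:

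- For admissions after 3 months, LOCF on the primary measures carries T1 and not baseline, so treating these patients as unchanged from baseline is not generally right.
- Scores may have recovered by T2 or T3, and inpatient days may lower recorded use on the TLFB. A full 1 SD worsening is an assumption.
- The article gives no basis for a difference in admissions between arms, and the 10% loss allowance may already include admissions.
- Only an inpatient stay triggers the rule. Relapses managed without admission stay in, so the relapse hypothesis remains testable, though incompletely.
- A reader might infer that harm would vanish from the safety conclusions. The Discussion sets no safety endpoint, admitted patients are still counted as dropouts, and adverse-event recording is commonly left to the full protocol, which is not shown.

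**Conclusion.** The concern holds in this form: a stated rule ends participation, in both arms, on a post-randomisation event close to the primary outcome, for a reason that concerns EMDR sessions only. The missing T2 and T3 data are informative under either reading, and the resulting bias can favour or disfavour EMDR.

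Its size cannot be known from the article. Under LOCF, a 10-point admission gap and true outcomes 0.5 to 1 SD worse than the carried values give 0.05 to 0.10 SD, that is 10% to 20% of the design effect of 0.5. The bias is about zero if admission rates and the shortfall g are equal in the two arms. The power figures of about 75% and 69% belong to the deletion reading alone and should not be added to the LOCF bias.

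Confidence is high that the rule needs changing and low on the magnitude. The case for change rests on the fact that uncollected outcomes cannot be recovered, not on any one scenario.

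**What to change.** Reconcile Dropouts and Follow-Up with Statistical Analysis by separating interruption of treatment from leaving the study:

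- Record an admission during the intervention period as an intercurrent event, not as exclusion or dropout.
- Keep the scheduled T1, T2 and T3 assessments for every randomised patient in both arms. The TLFB is retrospective, so days can be completed after discharge. Flag inpatient days and state how they enter the analysis.
- Analyse these patients as randomised, on their observed values, instead of carrying forward pre-admission values.
- Report admissions by arm and by cause. Only admissions for substance misuse should count towards the relapse hypothesis; an acute comorbid episode need not involve a relapse, and counting every admission would misclassify that outcome.

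Whether EMDR sessions stop or resume after an admission is a clinical matter for the investigators and is not addressed here.

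The cost is a protocol amendment and some visits that are harder to schedule. No new instrument and no extra patients are needed, and the target of 142 can stay.

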## Materials and Equipment

### Instruments and Measures

The consumption of substances will be quantified using the following tools (see Table 2):

Timeline Followback Questionnaire (TLFB): The TLFB (31) is a retrospective calendar-based measure of daily substance use, initially developed to obtain self-reports of alcohol use but nowadays also used for other substances.Severity of Dependence Scale (SDS): The SDS (32) is a 5-item questionnaire indicating the degree of dependence on different types of drugs. Each item is scored on a 4-point scale (0–3) and summed to create a total score. Higher scores indicate greater dependence.Visual Analog Scale (VAS): A self-report scale to measure craving intensity, classically used to measure pain intensity. It ranges from 0 to 10: the higher the score, the greater the craving severity.

**Table 2 T2:** Measurements to evaluate consumption symptoms.

**Clinical variable**	**Measurement interview/Self-report**	**T0**	**T1**	**T2**	**T3**
		**Baseline**	**Mid-treatment**	**Post-treatment**	**Post-treatment**
				**6 months**	**12 months**
Timeline	TLFB	x	x	x	x
Dependence	SDS	x	x	x	x
Craving	EVA	x	x	x	x

*TLFB, Timeline Followback Questionnaire; SDS, Severity of Dependence Scale; EVA, Visual Analog Scale*.

Trauma-related symptoms will be evaluated using the tools listed in Table 3:

Childhood Trauma Questionnaire (CTQ): The CTQ (36), Spanish validation (50), is a self-administered 28-item scale developed as a screening tool for histories of childhood abuse and neglect, with 5 subscales: emotional, physical or sexual abuse, and emotional or physical neglect. A 5-point Likert scale is used for the responses, ranging from “Never True” to “Very Often True.”Global Assessment of Posttraumatic Stress Questionnaire(EGEP-5): The EGEP-5 (51) is a clinical interview for the diagnosis of PTSD, both current and in the past, based on DSM-V criteria. This scale contains three sections: events, symptoms and functioning.The Holmes-Rahe Life Stress Inventory (37); Spanish validation (52): this is a scale assessing the frequency of 43 common stressful life events over the past 12 months, providing a standardized measure of their impact (53). Scores below 150 reflect low levels of stress, scores between 150 and 299 represent a 50% risk of a stress-related illness in the near future and scores above 300 represent an 80% risk (37), although each individual's reactions to stress and coping ability must be considered.Impact of Event Scale-Revised (IES-R): The IES-R (54), Spanish validation (55), is a 22-item self-report measure of subjective distress over the previous 7 days related to a specific stressful life event. Items correspond directly to 14 of the 17 DSM-IV symptoms of PTSD. Items are rated on a 5-point scale ranging from 0 and 4, yielding a total score ranging from 0 to 88, with subscale scores for Intrusion, Avoidance, and Hyperarousal.Dissociative Experiences Scale (DES): The DES (36), Spanish validation (56), is a 28-item self-reported questionnaire measuring a wide range of dissociative experiences, from normal to pathological, with an overall mean score ranging from 0 to 100 (57).

**Table 3 T3:** Measurements to evaluate psychological trauma symptoms.

**Clinical variable**	**Measurement interview/Self-report**	**T0**	**T1**	**T2**	**T3**
		**Baseline**	**Mid-treatment**	**Post-treatment**	**Post-treatment**
				**6 months**	**12 months**
Childhood T	CTQ	x			
PTSD	EGEP	x		x	x
Traumatic events	H-RLSI	x			
Trauma's impact	IES-R	x		x	x
Dissociation	DES	x		x	x

*Childhood T, Childhood trauma; CTQ, Childhood Trauma Questionnaire; PTSD, post-traumatic stress disorder; EGEP, Global Assessment of Posttraumatic Stress Questionnaire; H-RLSI, The Holmes-Rahe Life Stress Inventory; IES-R, Impact Event Scale; DES, Scale of Dissociative Experiences*.

Diagnosis, clinical symptoms, and functioning will be assessed using the following instruments (see Table 4):

The clinical diagnosis of SUD will be made according to DSM-5 criteria, using the Spanish version of the clinical interview Psychiatric Research Interview for Substance and Mental Disorders (PRISM) (42).Mini-International Neuropsychiatric Interview (MINI): A Spanish-validated brief structured diagnostic interview to assess the 17 most common psychiatric disorders as per DSM-IV criteria (58).Hamilton Depression Rating Scale (HDRS): The HDRS (38), Spanish validation (59), is a 17-item hetero-administered scale designed to be used in patients previously diagnosed with depression, to quantitatively assess the severity of and changes in depressive symptoms. Each item has three or five possible answers, scored 0–2 or 0–4, respectively. Total scores range from 0 to 52.Young Mania Rating Scale (YMRS): The YMRS (39), Spanish validation (60), is an 11-item hetero-administered scale which quantifies the severity of manic and hypomanic episodes. Four items are given more weight to compensate for poor cooperation from severely ill patients and are graded on a 0–8 scale (irritability, speech, thought content and disruptive/aggressive behavior), while the remaining seven items are graded on a 0–4 scale.Brief Psychiatric Rating Scale (BPRS): The BPRS (40), Spanish validation (61), is an 18-item hetero-administered scale measuring psychopathological changes. It includes anxious, affective and psychotic symptoms, with each rated on a severity scale of 1–7.Functioning Assessment Short Test (FAST): The FAST (41) is a 24-item instrument to evaluate functioning in six areas: autonomy, occupational functioning, cognitive functioning, finances, relationships and leisure. Each item is rated on a 4-point scale and summed to obtain a global score ranging from 0 to 72. The higher scores indicate poorer functional status.

**Table 4 T4:** Measurements to evaluate clinical symptoms and functionality.

**Clinical variable**	**Measurement interview/Self-report**	**T0**	**T1**	**T2**	**T3**
		**Baseline**	**Mid-treatment**	**Post-treatment**	**Post-treatment**
				**6 months**	**12 months**
Diagnosis	PRISM	x			
Diagnosis	MINI	x			
Mania	YMRS	x		x	x
Depression	HDRS	x		x	x
Psychiatric S.	BPRS	x		x	x
Functionality	FAST	x		x	x

*PRISM, Psychiatric Research Interview for Substance and Mental Disorders; MINI, Mini-International Neuropsychiatric Interview; YMRS, Young Mania Rating Scale; HDRS, Hamilton Depression Rating Scale; Psychiatric S, Psychiatric symptoms; BPRS, Brief Scale of Psychiatric Evaluation, FAST, Functioning Assessment Short Test; Psychiatric S, Psychiatric symptoms*.

